Based on previous studies, an intraclass correlation coefficient of 0.95 and a standard deviation (sd) for dental plaque and denture plaque of 0.75 and 0.88 respectively is used. A 25% improvement of oral hygiene level is the presumed effect of the intervention. With regard to the design effect and drop-outs, loss to follow up, and uncertainty in power calculation, a sample size of 360 residents and 12 clusters per country seems an achievable number for the 6-months period. This means 30 residents per (residential) care home.

To participate in the study, a resident should:

• Supply a written informed consent, undersigned by himself or his legal representative

• Have teeth and/or partial or complete dentures

• Have the cognitive and physical condition required for undergoing an oral examination

• Be residing in the institution during the entire 6-months period presumably.

Residents are excluded when in day-care, in short-term residency, in coma, in palliative care or terminally ill, using a denture adhesive, expressing verbal or physical resistiveness before or during an oral examination.

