### Statistical analysis

Both categorical and continuous variables are initially analyzed using exploratory data analysis, employing a variety of mostly graphical techniques and techniques for testing the necessary assumptions. The institution is the unit of randomization and the residents are the units of analysis. Cluster effects are addressed in the analysis. Intraclass correlation will be calculated for each outcome variable as a measure of correlation among residents within the institutions as well as among institutions within each country. The effect of the implementation project at individual, institution and country level is summarized and analyzed in a multilevel comparative analysis. Three comparative dimensions are handled simultaneously: the resident effect, the institution effect, and the country effect. Therefore, a three-level structure is used with resident (level 1) and institution (level 2), nested in broader organization units on country level (level 3). Differences in primary outcomes at baseline and differences between the intervention and the control group as well as between countries at baseline and at 6 month are calculated. Covariates at individual level are the subjects of the resident questionnaire and the nurse and nurse aide questionnaire.

Responses to the semi-structured interview of the process evaluation are analyzed using coding techniques commonly utilized for qualitative research methods [55]. Recurrent themes in the responses are used to set up a framework.

All research data are analyzed using MANOVA. A multilevel regression analysis is performed to determine the most important predicting factors with respect to oral hygiene level.

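### The plan names two incompatible analyses, a three-level model for the intervention effect and MANOVA for all data, and does not say which one tests the primary outcome

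*Protocol article*

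**What the plan says.** All of the method statements come from one section, Statistical analysis, in the protocol article.

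- On units: "The institution is the unit of randomization and the residents are the units of analysis". On clustering: "Cluster effects are addressed in the analysis". An intraclass correlation is to be calculated for each outcome.
- On the intervention effect: "The effect of the implementation project at individual, institution and country level is summarized and analyzed in a multilevel comparative analysis". The levels are resident, institution and country.
- At the end of the section: "All research data are analyzed using MANOVA". No dependent variables, home term, error stratum or restricted role are given.
- Immediately afterwards: "A multilevel regression analysis is performed to determine the most important predicting factors with respect to oral hygiene level". This regression is for finding predictors, not for testing the arms.

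Two other sections bear on the point. Under Participants and setting, a resident qualifies if they "Have teeth and/or partial or complete dentures", so some residents can have only one of the two plaque scores. Under Oral examination, natural teeth are scored 0-3 and dentures 0-4, with no composite. Research question 2 compares nurse attitude and knowledge between arms and is posed at care home level.

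**The concern.** The same primary data are covered by two methods that make opposite assumptions about independence. A multilevel model with a home effect allows residents of one home to resemble each other. Standard MANOVA on residents assumes that they do not, although homes were randomised. Research question 1 asks for a statistically significant difference, so the choice between the methods can decide the trial's answer, and either could later be reported as the one specified in the protocol.

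Two further consequences depend on how the MANOVA sentence is applied. If the two plaque indices were its joint outcomes, it would need both scores from each resident. For nurse outcomes, the described hierarchy has residents at level 1 and gives nurses no place, so the multilevel text does not clearly protect research question 2.

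**Working it through.** **Inputs from the protocol article.** There are 24 homes with 30 residents each: 12 × 30 = 360 per country and 24 × 30 = 720 in total, which agrees with the stated size. The design effect is Deff = 1 + (m − 1)ρ. The planning ICC is 0.95 and the significance level is 0.05.

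**Assumptions.** There are 12 homes per arm. ICCs of 0.05 and 0.10 are shown beside the plan's 0.95. The two plaque indices correlate at 0.3. The tests are two-sided.

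**Design effects at m = 30.** 1 + 29 × 0.05 = 2.45; 1 + 29 × 0.10 = 3.90; 1 + 29 × 0.95 = 28.55.

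**One outcome, clustering ignored.** The true false-positive rate is 2 × [1 − Φ(1.96/√Deff)]. For ICC 0.05, 1.96/√2.45 = 1.25, which gives 21%.

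**Two outcomes, clustering ignored.** If home effects share the between-index correlation, the large-sample rate is P(χ² with 2 df > 5.99/Deff) = exp(−2.996/Deff). For ICC 0.05, exp(−2.996/2.45) = 0.29.

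**Simulation.** Two-outcome resident-level Hotelling T² under the null, 12 homes per arm, with 3,000 to 6,000 replicates per setting. The ranges mainly reflect whether home effects are correlated across the two indices.

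| ICC | Deff | One outcome, formula | Two outcomes, formula | Two outcomes, simulated |
|---|---|---|---|---|
| 0.05 | 2.45 | 21% | 29% | 29-33% |
| 0.10 | 3.90 | 32% | 46% | 46-49% |
| 0.95 | 28.55 | 71% | 90% | 90-91% |

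At ICC 0 the simulated rate was 5.4%, as it should be. Tests on home means held about 5%. With only 6 residents per home contributing, the simulated two-outcome rates were 9-10%, 14-15% and 62-64% at the same three ICCs.

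**Residents lost if both indices were joint outcomes.** The share with both natural teeth and a denture is not given. For assumed shares of 10% to 50%, 720 × 0.10 = 72 to 720 × 0.50 = 360 residents are kept, and 648 to 360 are dropped.

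**Nurse outcomes.** Nurses per home and their ICC are not given, so no rate is calculated. The direction is the same if individual nurses are treated as independent.

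**The case against.** The strongest reply is that the plan does deal with clustering. The section says so outright, promises an ICC for each outcome and assigns the implementation effect to a multilevel analysis. The Discussion repeats that the random effect must be taken into account. The MANOVA sentence also cannot be meant literally, because the interview data are assigned to qualitative coding in the paragraph before it. It may be only a loose summary, and nothing says that it supplies the confirmatory test.

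Much of this stands. A reader might infer that the plan ignores clustering by home; the text does not support that. A reader might also infer that every resident lacking either natural teeth or a denture is excluded. That does not follow either. The dependent variables of the MANOVA are not named, and they could be the baseline and 6-month scores of a single index. The separate scales, and the separate standard deviations in the sample size text, are compatible with separate analyses. On nurses, the care-home-level wording of research question 2 may point to an analysis of home means. A MANOVA on home means, or one with home as the error stratum, could be valid.

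The reply does not remove the conflict. No such MANOVA is described, the sentence carries no restriction, and the one regression named after it has a different purpose. Nor is this detail that an article leaves to an analysis plan: the article states a rule, and that rule conflicts with the rest of its section.

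**Conclusion.** The point holds as an unresolved contradiction that should be corrected before analysis. The section names a multilevel analysis and an unqualified MANOVA for the same data, without saying which tests the primary effect.

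The error rates are conditional on a single-level, two-index MANOVA of residents being that test. On that condition, the false-positive rate is about six times nominal at an ICC of 0.05, so the conclusion does not rest on the planning value of 0.95, whose plausibility is a separate matter. The loss of residents with one index needs the further, unstated premise of a joint outcome vector, and its size rests on an assumed dentition share. For nurse outcomes the gap is more direct, because MANOVA is the only named test that covers them, subject to the care-home-level wording of research question 2.

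**What to change.** 1. Delete the MANOVA sentence or restrict it to descriptive use.
2. State that the multilevel model with a random home effect is the primary test of the intervention effect.
3. Fit it separately for each plaque index, using all residents who have that index. Adjusting for the baseline index, which is already collected, and basing inference on the number of homes are preferable. The particular degrees-of-freedom method can be left to the analysis plan.
4. Analyse nurse knowledge and attitude with nurses nested in homes, or on home-level means, in line with research question 2.

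The cost is wording only: no additional homes, residents or measurements. Standard errors will be larger than under a resident-level MANOVA, and will then reflect the randomisation of homes.

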## Discussion

A cluster randomized controlled trial allows for statistical analysis of the feasibility and effectiveness of an intervention on care provision. This trial provides both practical and methodological advantages for implementation studies, especially when the intervention requires policy or behavioural alterations and intends an effect at institution level [56]. Cluster randomization using institutions as the unit of randomization reduces contamination between groups of persons. It is easier to deliver an intervention at institution level (unit) than at individual level within an institution. Also, when focussing on all nurses, nurse aides, and residents, group dynamics and peer pressure may facilitate the adoption of the intervention. On the other hand, cluster randomization may result in a random effect, which has to be taken into account when analyzing and interpreting the results. Another problem of cluster randomization is the hazard of selection bias at cluster level. An institution which, for one or another reason, decides to abandon the study may cause an important attrition bias. This is even of greater concern in case of drop outs of differential institutions in the intervention as well as in the control group. To prevent drop-out, all participating institutions are requested to provide a written informed consent for the entire study and study period.

The level of oral hygiene as primary outcome measure, a set of explanatory variables at different levels (resident, institution, and country), and the process evaluation data will allow revealing the supervised implementation effect and the stimulating and inhibiting factors.

An essential objective of the implementation project is to improve the oral health knowledge and the oral health care attitude and skills of the nurses and nurse aides. Many guidelines are, because of their lengthy and detailed character, rather difficult to access for nurses and nurse aides. The guideline used in this study provides also an easy to use daily oral health care protocol derived from the guideline, enabling the nurses and nurse aides to adhere the instructions and recommendations more easily.
